**Study rater completed, together with the patient**				
Demographics / social data		X		
Motor symptoms	MDS-UPDRS, part III (47)	X		
Non-motor symptoms	MDS-Non-Motor Rating Scale (MDS-NMS) (48)	X	X	X
Cognition	Montreal Cognitive Assessment (MoCA) (49)	X		
Comorbidity	Charlson Comorbidity Index (CCI) (50)	X		
Care coordination	Modified Nijmegen Continuity Questionnaire	X	X	X
	(mNCQ) (51)			
	Interview questions^***^	X	X	X
Feasibility of the intervention^**^	Feasibility checklist		X	
(Serious) adverse events	Interview questions		X	X
**Study rater completed, together with the FC**				
Demographics		X		
Resource utilisation	Resource Utilisation questionnaire (RUD) (52), adapted for PD	X	X	X
[if applicable] Quality of the end-of-life experience of the patient^*^	Quality of Dying and Death questionnaire (QoDD) (53)		X	X
**Questionnaires completed by the patient independently**				
Disease-specific symptoms	Edmonton Symptom Assessment Scale for Parkinson's Disease (ESAS-PD) (54)	X	X	
Depression	Beck Depression Inventory (BDI-I) (55)	X	X	
Quality of life	PDQ-39 (56)	X	X	X
Self-rated health	EQ-5D-5L (57)	X	X	X
Palliative-phase symptom severity	Integrated Palliative Care Outcome (IPOS) (58)	X	X	X
Experienced quality of care (including the intervention)	Short Assessment of Patient Satisfaction (SAPS) (59)	X	X	
Experienced involvement in decision making	CollaboRATE (60)	X	X	
**Questionnaires completed by the FC independently**				
Quality of life	EQ-5D-5L (57)	X	X	X
	PQoL Carer (61)	X	X	X
**Study rater competed**				
ACP documentation	Chart review	X	X	X
[if applicable] Place of death: preferred and actual	Chart review		X	X
**Interview with patient and FC**				
Feasibility of the intervention**/^***^	Interview guide		X	
Experienced quality of care, quality life, and end-of-life issues^***^	Interview guide			X
**Quantitative motor symptom assessment**				
Motor symptom assessment^***^	PDMonitor	X	X	X

*
*in case the patient dies during follow-up;*

**
*intervention group only;*

*** *Optional element of the study protocol; T0, Baseline after inclusion; T1, 6 months after randomisation (intervention completed); T2, 12 months after randomisation (long-term follow-up)*.

### Statistical Analysis

#### Primary Endpoint

To evaluate the effectiveness of the intervention, all analyses of endpoints will be done in the intent-to-treat population. The primary efficacy analysis will be to investigate the effect of the PD_Pal intervention on the percentage of patients with documented ACP decisions from baseline to month 6 in the intervention and care-as-usual group. This will be tested by means of the Mantel Haenszel estimate method and by using multilevel logistic regression model, with data clustered within countries and with categorical factors (groups) and baseline characteristics as covariates, in order to test which independent variables (indicators) contribute to the effect of the intervention. The primary analysis will be repeated for the t2 assessment (12 months after randomisation) and also using the per-protocol population to confirm the overall study results. All tests will be performed two-sided, and *P*-values < 0.05 will be considered statistically significant.

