### Sample Size Calculation

We assume that 5% of the target population will have documented ACP wishes at baseline. The study is powered to show a 20% absolute increase from a baseline of 5% (control group) in the primary outcome measure, that is, documented ACP-decisions, at 6 months, with a power of 0.80, a statistical significance of 0.05 (two sided) and an intraclass correlation coefficient (correcting for clustering within countries) of 0.10, by a Fisher's exact test. With the above assumptions, 74 patients in each treatment group are required. The sample size will be increased to 93 patients in each treatment group for allowing a 25% dropout rate within the 6-month follow-up period for the primary outcome effectiveness evaluation.

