#### Gender-Specific Analyses

We will undertake a planned subgroup analysis for the primary outcome measure, separately for women and men.

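### The primary model, as described, tests which baseline characteristics predict documented ACP, not which ones change the effect of the intervention, although the latter is its stated purpose

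*Protocol article*

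**What the plan says.** The protocol article, Statistical Analysis, Primary Endpoint, says that the effect on documented ACP at month 6 will be tested "by means of the Mantel Haenszel estimate method and by using multilevel logistic regression model, with data clustered within countries". The model contains group as a categorical factor and "baseline characteristics as covariates, in order to test which independent variables (indicators) contribute to the effect of the intervention". The same paragraph makes all tests two-sided with significance at P<0.05. The baseline characteristics are not listed.

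The only other place that looks at the effect in parts of the population is Gender-Specific Analyses: "We will undertake a planned subgroup analysis for the primary outcome measure, separately for women and men". It states no comparison of the two sexes' effects. The article nowhere mentions a group-by-covariate interaction.

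**The concern.** One sentence gives both a model and the question the model is meant to answer, and the two do not match. Asking which variables contribute to the effect of the intervention has as its null that the intervention effect is the same at every level of the variable. The coefficient of a covariate entered alongside group has a different null: that the variable is unrelated to documented ACP, with one coefficient shared by both arms.

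If the sentence is followed as written, significant covariates would be reported as factors in the intervention's effect. A variable that merely predicts documentation (age, stage and cognition are possible examples) could be named although it does not change the effect. A variable that does change the effect could go unmentioned. At stake is what the trial says about for whom the intervention works.

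**Working it through.** **No figure to reproduce.** The plan attaches no number to this clause. Its sample-size figures serve below only as trial sizes; how they were derived does not bear on this point.

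**What each coefficient tests.** As described, for group g and covariate x within a country:

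logit P(documented) = a + b·g + c·x + country effect

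The log odds ratio for the intervention is b at x = 0 and b at x = 1. The test of c = 0 therefore carries no information on whether the effect differs. With an interaction added,

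logit P(documented) = a + b·g + c·x + d·g·x + country effect,

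the log odds ratio is b at x = 0 and b + d at x = 1. The stated question is a test of d = 0.

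**Inputs from Sample Size Calculation.** Control rate 5%; intervention rate 5% + 20 points = 25%; country intraclass correlation 0.10; 74 per arm required and 93 per arm recruited; 25% dropout, so 93 × 0.75 = 69.75, about 70 evaluable per arm. There are seven countries (Study Design).

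**Assumed, because the document gives none.** A binary covariate with 50% prevalence, and the covariate effects shown below.

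**Purely prognostic covariate (same intervention odds ratio at both levels).** Random-intercept logistic model, country SD = √[(0.10/0.90) × π²/3] = 0.605, likelihood-ratio tests at 0.05, 600 simulated trials per row:

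| Per arm | Prognostic odds ratio | Main-effect test rejects | Interaction test rejects |
|---|---|---|---|
| 70 | 2 | 29% | 7% |
| 70 | 3 | 53% | 5% |
| 70 | 4 | 76% | 4% |
| 93 | 2 | 35% | 9% |
| 93 | 3 | 69% | 7% |
| 93 | 4 | 87% | 5% |

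A repeat with ordinary logistic models (no country effect, 2,000 trials each) gave main-effect rates of 30, 57 and 78% at 70 per arm and 37, 70 and 86% at 93, with 4 to 7% for the interaction. A further run at 74 per arm with odds ratio 3 (1,000 trials) gave 61% against 6%. At 740 per arm (300 trials) it gave 100% against 4%, so a larger trial makes the false attribution more certain.

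**True modifier with no average association.** Two sets of assumed rates:

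- Milder: control 2% and 8%, intervention 28% and 22% at x = 0 and x = 1. Averages over arms are (2 + 28)/2 = 15% and (8 + 22)/2 = 15%. Interaction odds ratio: [(0.22/0.78)/(0.28/0.72)] / [(0.08/0.92)/(0.02/0.98)] = 0.725/4.26 = 0.17, or about 6-fold. At 74 per arm: main effect 5%, interaction 32%.
- Stronger: control 9% and 1%, intervention 20% and 30%. Averages are 14.5% and 15.5%. Interaction odds ratio: [(0.30/0.70)/(0.20/0.80)] / [(0.01/0.99)/(0.09/0.91)] = 1.714/0.102 = 16.8. At 70 per arm: main effect 8%, interaction 53%. At 93 per arm: 7% and 64%.

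**True modifier with flat control rates.** Control 5% and 5%, intervention 15% and 35%; interaction odds ratio (0.35/0.65)/(0.15/0.85) = 3.05. At 74 per arm: main effect 40%, interaction 17%. Here the main-effect test does flag a real modifier.

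**Events available.** 70 × 0.05 + 70 × 0.25 = 3.5 + 17.5 = 21.

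**The case against.** The strongest reply is that the article never says the covariates enter as main effects only. A reader might infer that from the missing interaction term, but it would be an inference from the silence of a condensed article; a fuller protocol or analysis plan, not shown, may contain interactions. That stands. What remains is that the published sentence assigns to the covariates a purpose that covariates, as described, do not serve.

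Second, the clause may be loose wording for predictors of documented ACP. Model and purpose then agree and only the reference to the intervention effect is wrong. The separate analysis by sex under its own heading fits this reading. It cannot be excluded, and the fix allows for it.

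Third, a reader might conclude that the analysis will name the wrong factors. The documents do not support that: the result depends on unknown covariate effects, and with flat control rates the main-effect test found the true modifier more often than the interaction test did. It can mislead; it need not.

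Fourth, the size of the missed-modifier problem depends on the scenario. The stronger case has an interaction odds ratio near 17 and a 1% cell with about 35 × 0.01 = 0.35 expected events at 70 per arm, where a likelihood-ratio test is fragile. Its gap of about 45 points (53 − 8) should not be quoted alone; the milder case gives 27 (32 − 5).

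Fifth, a reader might infer that these covariate tests will steer how the intervention is tailored. No section says so. Other Endpoints places country-specific tailoring with feasibility, and Other Study Parameters bases enhancement on interviews linked with quantitative data.

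Finally, a factor with a common odds ratio generally does shift the absolute risk difference. True, but the covariate coefficient is not a test of that shift either.

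**Conclusion.** The point holds as a mismatch between the stated purpose and the model as described, and it is worth correcting. Following the sentence as written would mean reading prognostic coefficients at P<0.05 as evidence on effect modification. The article states its Bonferroni correction for the secondary outcome measures, not for these tests.

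The sizes are illustrative. They assume a binary covariate with 50% prevalence, the covariate effects listed, and modification defined on the odds-ratio scale of the model. The 2 to 4 range of prognostic odds ratios and both modifier scenarios are assumptions. The direction of the first result does not depend on them: any truly prognostic variable raises the main-effect rejection rate above the nominal level without any effect modification.

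The comparison of intervention with usual care, by Mantel-Haenszel or by the adjusted model, is not affected.

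**What to change.** In Statistical Analysis, Primary Endpoint, state that the baseline characteristics are included for adjustment and that their coefficients are not read as contributions to the intervention effect. Replace the purpose clause with wording such as: Whether a baseline characteristic modifies the effect of the intervention will be examined by adding a group-by-characteristic interaction to the model, one characteristic at a time, for a short prespecified list that includes sex; each will be reported as an estimate with its 95% confidence interval and labelled exploratory.

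If predictors of documentation were meant, reword the clause to say so and drop the reference to the intervention effect. If the full analysis plan already contains interactions, the clause need only be aligned with it.

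The cost is a sentence or two and a few extra model fits, with no new data or patients. The downside is that interaction estimates will be imprecise with about 21 expected events (power was 17 to 32% at 74 per arm in the scenarios with interaction odds ratios of about 3 to 6), so less can be claimed about which factors drive the effect.

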#### Secondary Endpoints

All secondary study parameters, except for the healthcare utilisation data, will be analysed similarly to the primary outcome parameter, except that for the secondary outcome measures we will correct for multiple testing (Bonferroni adjustments). For the healthcare utilisation data, the primary analysis will be from a health and social care cost perspective, with secondary analyses from a societal perspective.

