## Abstract

**Background:** Parkinson's disease (PD) is a progressive neurodegenerative disease with motor- and non-motor symptoms. When the disease progresses, symptom burden increases. Consequently, additional care demands develop, the complexity of treatment increases, and the patient's quality of life is progressively threatened. To address these challenges, there is growing awareness of the potential benefits of palliative care for people with PD. This includes communication about end-of-life issues, such as Advance Care Planning (ACP), which helps to elicit patient's needs and preferences on issues related to future treatment and care. In this study, we will assess the impact and feasibility of a nurse-led palliative care intervention for people with PD across diverse European care settings.

**Methods:** The intervention will be evaluated in a multicentre, open-label randomized controlled trial, with a parallel group design in seven European countries (Austria, Estonia, Germany, Greece, Italy, Sweden and United Kingdom). The “PD_Pal intervention” comprises (1) several consultations with a trained nurse who will perform ACP conversations and support care coordination and (2) use of a patient-directed “Parkinson Support Plan-workbook”. The primary endpoint is defined as the percentage of participants with documented ACP-decisions assessed at 6 months after baseline (t1). Secondary endpoints include patients' and family caregivers' quality of life, perceived care coordination, patients' symptom burden, and cost-effectiveness. In parallel, we will perform a process evaluation, to understand the feasibility of the intervention. Assessments are scheduled at baseline (t0), 6 months (t1), and 12 months (t2). Statistical analysis will be performed by means of Mantel–Haenszel methods and multilevel logistic regression models, correcting for multiple testing.

**Discussion:** This study will contribute to the current knowledge gap on the application of palliative care interventions for people with Parkinson's disease aimed at ameliorating quality of life and managing end-of-life perspectives. Studying the impact and feasibility of the intervention in seven European countries, each with their own cultural and organisational characteristics, will allow us to create a broad perspective on palliative care interventions for people with Parkinson's disease across settings.

**Clinical Trial Registration:**www.trialregister.nl, NL8180.

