### Study Endpoints

#### Primary Endpoint

The primary endpoint is defined as the percentage of participants with documented ACP decisions in at least one of the patients' medical records assessed at 6 months (t1) after baseline. We believe it is important to choose an outcome measure that is as close as possible to the intervention. The choice of documentation of ACP decisions as the primary endpoint was prompted by a number of considerations. One of these is that even though discussing ACP is a crucial part of the intervention, such a discussion by itself does not ensure better care, and adequate documentation is therefore a further prerequisite. Another consideration is that this endpoint proved to be sensitive to change in similar interventions targeting other populations (40).

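### The rule for secondary outcomes carries a binary-endpoint analysis over to scale scores; read literally it needs cut-points that are not given and loses substantial power

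*Protocol article*

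**What the plan says.** The primary endpoint (Study Endpoints, Primary Endpoint) is binary: the "percentage of participants with documented ACP decisions in at least one of the patients' medical records assessed at 6 months (t1"). Under Statistical Analysis, Primary Endpoint, the effect on it is to be "tested by means of the Mantel Haenszel estimate method and by using multilevel logistic regression model, with data clustered within countries", with group and baseline characteristics in the model.

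Under Statistical Analysis, Secondary Endpoints, the rule is: "All secondary study parameters, except for the healthcare utilisation data, will be analysed similarly to the primary outcome parameter". Apart from the healthcare utilisation data, the one stated difference is that "for the secondary outcome measures we will correct for multiple testing (Bonferroni adjustments"). The Abstract describes the trial's statistics in the same terms: "Statistical analysis will be performed by means of Mantel–Haenszel methods and multilevel logistic regression models, correcting for multiple testing".

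The secondary endpoints concern patients' and caregivers' quality of life, care coordination, patients' symptom burden and cost-effectiveness. In Table 2 all but the last are measured by rating scales or questionnaires:

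- at t0, t1 and t2: MDS-NMS, mNCQ, PDQ-39, EQ-5D-5L (patient and caregiver), "Integrated Palliative Care Outcome (IPOS") and PQoL Carer;
- at t0 and t1: ESAS-PD and BDI-I, as well as SAPS and CollaboRATE, which cover satisfaction and involvement in decisions.

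The article gives no cut-point, no responder definition and no model for a score.

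**The concern.** A Mantel-Haenszel estimate and a logistic model in their usual form take a yes/no outcome. The article extends them to every secondary parameter, makes two explicit exceptions (utilisation data and the multiplicity correction), and does not except scale scores. An analyst who follows the sentence as written must turn each score into two categories. The article does not say where to cut, so the cut would be chosen later, and splitting a score throws away information.

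These outcomes are the part of the effectiveness question that patients and caregivers feel directly. The trial is sized for the binary endpoint only, so their power is unplanned to begin with, and a Bonferroni penalty is added. An avoidable loss here could leave a real benefit on quality of life or symptom burden undetected.

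**Working it through.** **The plan's own figure.** The article states no power, SD or target difference for any secondary outcome, so there is nothing to reproduce. Effect sizes, normality and correlations below are assumptions.

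**Inputs.**
- Patients per arm at t1: 93 enrolled with 25% dropout (Sample Size Calculation), so 93 × 0.75 = 69.75, about 70. The article's own evaluable figure is 74.
- Two-sided alpha 0.05 (Statistical Analysis), critical value 1.96.
- Assumed: normal score, difference d = 0.4 SD, baseline-to-follow-up correlation r = 0.6.
- Country clustering is left out of both sides of each comparison.

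**Unadjusted, score kept continuous.** z = d × √(n/2) = 0.4 × √35 = 2.366. Power = Φ(2.366 − 1.96) = 0.66.

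**Unadjusted, split at the pooled median.** The proportions are Φ(−0.2) = 0.421 and Φ(0.2) = 0.579, a difference of 0.1585. The standard error is √(2 × 0.421 × 0.579 / 70) = 0.0834, so z = 1.90. Power = Φ(1.90 − 1.96) = 0.48 (0.47 with a pooled variance). For small effects a median split keeps 2/π = 0.64 of the information.

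**Baseline-adjusted, continuous.** z = 2.366 / √(1 − 0.6²) = 2.366 / 0.8 = 2.958. Power = Φ(2.958 − 1.96) = 0.84.

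**Baseline-adjusted, dichotomised.** This is a logistic model on the median-split outcome with the continuous baseline score as covariate. A simulation of 20,000 trials with the same inputs gave 0.57 (Wald test) and 0.58 (likelihood-ratio test); other runs gave 0.56 and 0.59. I quote 0.56 to 0.59.

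| | Dichotomised | Continuous |
|---|---|---|
| Unadjusted | 0.48 | 0.66 |
| Adjusted for baseline | 0.56–0.59 | 0.84 |

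**Dependence on the cut.** Take 74 per arm and the difference that the continuous score detects with 80% power, d = 0.461. A median split has power 0.60 and would need 118 per arm for 80%. If the event is defined by the upper 30%, 20% or 10% of controls, power is 0.59, 0.54 or 0.43. The median split is the most favourable of the cuts tried.

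**Dependence on the assumed difference** (74 per arm, unadjusted, median split). For d = 0.3, 0.4 and 0.5, power is 0.45, 0.68 and 0.86 continuous against 0.30, 0.49 and 0.67 dichotomised.

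**If an ordinal or rank form was meant.** Its efficiency against a normal-theory analysis is about 0.955 under normality. Then z = 2.366 × √0.955 = 2.312 and power is 0.64 against 0.66. The loss nearly vanishes.

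**The case against.** The strongest defence is that the article says the secondary analyses are similar to the primary one, not identical. That can mean the same intention-to-treat population, country clustering, baseline covariates, two-sided tests and repeat at t2, with a model suited to each scale. Both named families also have forms for ordered scores that need no cut-point: the stratified mean-score Mantel-Haenszel test and proportional-odds regression. Nowhere does the article announce dichotomisation, and a full analysis plan may name linear models.

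Much of this stands, and it rules out several stronger conclusions that a reader might draw:

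- *That the rule cannot be carried out.* Ordinal extensions exist, so this goes too far.
- *That the analysis would be invalid.* With a prespecified cut, a dichotomised comparison keeps its type I error; what it loses is power.
- *That the baseline score is discarded.* The primary analysis already allows baseline characteristics as covariates, and a logistic model can take a continuous baseline score. The fair adjusted comparison is therefore 0.56–0.59 against 0.84, not 0.48 against 0.84.
- *That Bonferroni is an error.* It controls the familywise error. Holm does so too and is never less powerful, but its gain depends on how many outcomes truly improve. With 11 outcomes (assumed: one test per instrument listed above), correlation 0.4 and d = 0.5, average power is 0.66–0.67 against 0.55 if all 11 effects are real, but 0.56 against 0.55 if only three are.

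The defence does not remove the point itself. The article is not silent; it states a rule for all secondary parameters, lists exceptions, and leaves scale scores inside the rule. A Mantel-Haenszel estimate alongside a logistic model most naturally describes a binary analysis, and the Abstract names nothing else. If a suitable model was intended, the sentence still has to say so.

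**Conclusion.** The point holds as a stated rule that does not fit the outcomes it covers. On a literal reading, the scale-score secondary endpoints would be split at unspecified cut-points. Under the assumptions shown, that costs about 18 percentage points of power unadjusted (0.66 − 0.48) and about 25 to 28 points with baseline adjustment (0.84 − 0.59 to 0.84 − 0.56). Less central cuts cost more. The size rests on normal scores, a 0.4 SD difference, a correlation of 0.6 and the dichotomised reading; on an ordinal reading it is about 2 points.

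The primary endpoint, its analysis and its sample size are untouched, and false-positive control for the secondary outcomes is not at issue.

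**What to change.** Replace the sentence on secondary parameters with wording such as:

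> Secondary scale outcomes will be analysed as scores with a multilevel linear model (ordinal where suited), using t1 and t2 where both are collected, with group, visit, group-by-visit, country and the baseline score. Mantel-Haenszel and logistic methods are used only for binary secondary outcomes.

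For instruments collected only at t0 and t1, the visit terms drop out. The existing exception for healthcare utilisation stays, and the Abstract should be brought into line.

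The cost is wording only. Table 2 already collects every one of these scores at t0, so no new data are needed. Moving from Bonferroni to Holm is optional; it makes simultaneous confidence intervals less simple, and the gain is small unless most secondary outcomes truly improve.

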#### Secondary Endpoints

Secondary endpoints relate to the expectation that patients and their FCs will experience a better quality of life, improved care coordination, and a reduced patient symptom burden and that FC will experience an improved quality of life, in a cost-effective manner.

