### Assessment Scheme

The baseline assessment (t0) consists of an in-person interview performed by the study assessor. The baseline assessment takes place either in the outpatient clinic setting, at the patient's home, or remotely via a video connection. In addition, the patient and FC complete a set of questionnaires that are self-administered. Within 2 weeks after the baseline assessment, a participant is randomized to either the intervention or the control group. For all participants, two follow-up assessments are thereafter foreseen (t1 and t2). After completion of the t2 assessment, the patient and FC will be invited for an optional semi-structured interview about end-of-life issues. Table 2 presents all assessments and the instruments that will be used to evaluate the (cost-)effectiveness and feasibility of the PD_Pal intervention.

**Table 2 T2:** Overview of the assessment schedule and its instruments, to evaluate the (cost-) effectiveness and feasibility of the PD_Pal intervention.

**Scales/domains**	**Instruments**	**Application at**		
		**T0**	**T1**	**T2**

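### Plain Bonferroni for the secondary outcomes is valid but inefficient: Holm's procedure over the same family controls the same error and never rejects less

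*Protocol article*

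**What the plan says.** In the protocol article, Statistical Analysis, Secondary Endpoints sets the scope as "All secondary study parameters, except for the healthcare utilisation data, will be analysed similarly to the primary outcome parameter", and then adds that "for the secondary outcome measures we will correct for multiple testing (Bonferroni adjustments". No number of tests, adjusted significance level or time point is attached to the correction. The primary-endpoint paragraph just before it sets the level at 0.05 and says "All tests will be performed two-sided".

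Study Endpoints, Secondary Endpoints describes constructs and not instruments: "patients and their FCs will experience a better quality of life, improved care coordination, and a reduced patient symptom burden", followed by caregiver quality of life and cost-effectiveness. The Abstract gives the same list: "Secondary endpoints include patients' and family caregivers' quality of life, perceived care coordination, patients' symptom burden, and cost-effectiveness". That makes four constructs apart from cost: patient quality of life, caregiver quality of life, care coordination and symptom burden.

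Table 2 lists more scales than constructs. It is introduced with the words "Table 2 presents all assessments and the instruments that will be used to evaluate the (cost-)effectiveness and feasibility of the PD_Pal intervention" and does not mark which scales are secondary endpoints. The only sample-size statement, "74 patients in each treatment group are required", concerns the primary endpoint. No power is stated for any secondary outcome.

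**The concern.** Single-step Bonferroni compares every p-value with 0.05 divided by the number of tests, even after some hypotheses in the family have been rejected. Holm relaxes the threshold after each rejection and pays nothing in family-wise error for doing so. Choosing Bonferroni therefore gives up power without buying extra error control.

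The claims on quality of life, care coordination and symptom burden rest on these tests. The trial is sized for a documentation endpoint and not for scale scores, so power on the secondary outcomes may be limited. The primary endpoint is not affected.

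**Working it through.** **Error control and dominance, for any family size.** Order the m p-values as p(1) ≤ … ≤ p(m). Bonferroni rejects when p ≤ 0.05/m. Holm rejects p(j) in sequence as long as p(j) ≤ 0.05/(m − j + 1).

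- *Never fewer rejections.* 0.05/m ≤ 0.05/(m − j + 1) at every step, so any p-value that passes Bonferroni, and every smaller one, also passes Holm.
- *Same family-wise error.* Suppose m0 hypotheses are truly null. The first true null that Holm rejects is met at step m − m0 + 1 at the latest, so its p-value is at most 0.05/m0. The probability that any of m0 null p-values is that small is at most m0 × 0.05/m0 = 0.05. Like Bonferroni, this needs no assumption about correlation.

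**Inputs for the size of the gain.** The document states no secondary power figure to reproduce.

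- Patients per arm: Sample Size Calculation recruits 93 and allows 25% dropout; 93 × 0.75 = 69.75, taken as 70.
- Level: 0.05, two-sided.
- Family size: not stated. Counting the non-cost scales in Table 2 that can be compared between arms at 6 months gives 11: MDS-NMS, mNCQ, ESAS-PD, BDI, PDQ-39, patient EQ-5D-5L, IPOS, SAPS, CollaboRATE, caregiver EQ-5D-5L and PQoL Carer. Seven of these repeat at 12 months, which would make 18. One test per named construct makes 4.
- Effect of 0.4 or 0.5 SD and correlation 0.5 between outcomes: assumptions.

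**Bonferroni power per outcome** (two-sample t-test, 70 per arm, level 0.05/m):

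| m | level | 0.4 SD | 0.5 SD |
|---|---|---|---|
| 1 | 0.05 | 0.652 | 0.836 |
| 4 | 0.0125 | 0.437 | 0.665 |
| 11 | 0.00455 | 0.307 | 0.531 |
| 18 | 0.00278 | 0.254 | 0.468 |

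**Bonferroni against Holm in the same family** (average power over truly affected outcomes, 0.4 SD, 70 per arm, correlation 0.5, 200,000 simulations). The simulation uses a normal approximation, so its Bonferroni values lie about one point above the t-test table.

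| Family | true effects | Bonferroni | Holm | gain (points) |
|---|---|---|---|---|
| 11 | 1 | 0.320 | 0.320 | 0 |
| 11 | 4 | 0.320 | 0.334 | 1.4 |
| 11 | 8 | 0.317 | 0.359 | 4 |
| 11 | 11 | 0.318 | 0.397 | 8 |
| 4 | 2 | 0.447 | 0.466 | 2 |
| 4 | 4 | 0.446 | 0.527 | 8 |

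At 0.5 SD and a family of 11 the gain is about 2 points with four true effects (0.545 to 0.566) and 12 with all eleven (0.548 to 0.664). Simulated family-wise error stayed below 0.05 for both methods in every scenario that contained a true null.

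**Restricting the family is a different operation.** Suppose four tests are run at 0.0125 and the other seven scales are tested at 0.05. With independent tests, the chance of at least one false positive over all eleven is 1 − (1 − 0.0125)^4 × (1 − 0.05)^7 = 1 − 0.951 × 0.698 = 0.336.

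**The case against.** Bonferroni is valid, simple and conservative, and nothing in the document is contradictory. It also yields simultaneous confidence intervals directly, which Holm does not. Holm's gain is small unless many outcomes truly improve. All of this stands, and it limits the point to an efficiency suggestion.

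Three stronger readings are tempting, and the document does not support them.

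- *That the correction runs over every instrument in Table 2.* The text refers to secondary outcome measures and gives no divisor. The secondary endpoints are defined as constructs, and scales such as SAPS and CollaboRATE match none of them by name. The divisors 11 and 18 are counts made for this check. A condensed article commonly leaves the family to the full protocol or the SAP, so its absence here is no finding.
- *That a smaller family would save power at the same error rate.* This is true of Holm only. Moving from 11 tests to 4 keeps 0.05 for those four and removes protection from the rest, as the 0.336 shows. The constructs also cover at least eight scales, so reaching four means choosing one instrument per construct, which changes what is being claimed.
- *That a moderate real benefit would usually be missed.* This depends on one assumed effect size. With 11 tests, power is 0.31 at 0.4 SD but 0.53 at 0.5 SD. The planned models include baseline characteristics as covariates. If the baseline score is among them and correlates 0.5 to 0.7 with follow-up, power with 11 tests is 0.44 to 0.67 at 0.4 SD and 0.70 to 0.89 at 0.5 SD.

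**Conclusion.** The point holds as a minor improvement. The article prespecifies plain Bonferroni, and Holm dominates it at the same family-wise error whatever the family turns out to be. That conclusion needs no assumption about effect size or correlation.

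The size of the benefit does depend on assumptions. At 70 per arm, 0.4 SD and correlation 0.5 it runs from nothing (one true effect) to about 8 points of average power (all outcomes affected). It is 1 to 2 points when only some outcomes are affected: four of eleven, or two of four. The upper figure is a best case and should not be read as the expected gain. The document does not show that power is being lost through an over-wide family.

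**What to change.** In Statistical Analysis, Secondary Endpoints, replace the Bonferroni adjustment by Holm's step-down adjustment over the same family of secondary tests. Report Holm-adjusted p-values: with m tests, the adjusted value for p(j) is the largest of (m − k + 1) × p(k) over k ≤ j, capped at 1.

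The cost is one line of analysis text and less simple interval reporting. Report Bonferroni or unadjusted confidence intervals beside the Holm p-values, say which, and note that a Bonferroni interval may include no effect where Holm rejects.

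Optionally, name one instrument and one time point per secondary construct as the tested family. This lowers the divisor, but the remaining scales and time points lose their error protection. They would have to be labelled exploratory and reported as estimates with confidence intervals. The choice of instruments is substantive and would need to be made before outcome data by arm are seen.
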